# Mesenteric excision surgery or conservative limited resection in Crohn’s disease: study protocol for an international, multicenter, randomized controlled trial

**DOI:** 10.1186/s13063-020-4105-x

**Published:** 2020-02-21

**Keywords:** Crohn’s disease, Ileocolic resection, Mesentery, Postoperative recurrence

## Abstract

**Background:**

The structures of the mesentery including adipose tissue, nerves, and lymphatics play an important role in the pathogenesis and disease progression of Crohn’s disease (CD). Conventional surgical resection for CD usually does not involve resecting the mesentery en bloc with the specimen. This contrasts with complete mesocolic excision (CME) in colorectal cancer, which involves radical resection of the mesentery. Preliminary evidence from smaller studies suggests that applying the principle of mesocolic excision to CD surgery may reduce the risk of postoperative recurrence. This randomized controlled trial is designed to test whether applying the principles of mesocolic excision to CD results in reduced postoperative recurrence. It also aims to evaluate intra- and postoperative morbidity between the two approaches.

**Methods:**

This international, multicenter, randomized controlled trial will randomize patients (*n* = 116) scheduled to undergo primary ileocolic resection to either receive extensive mesenteric excision (EME) or conventional ileocolic resection with limited mesenteric excision (LME). Five sites will recruit patients in three countries. In the EME group, the mesentery is resected following CME, while avoiding the root region, i.e., 1 cm from the root of the ileocolic artery and vein. In the LME group, the mesentery is retained, i.e., “close shave” or < 3 cm from the border of bowel. The primary end point will be surgical recurrence after surgery. The secondary end points will be the postoperative endoscopic and clinical recurrence, and intra- and postoperative morbidity. Demographics, risk factors, laboratory investigations, endoscopy, postoperative prophylaxis and imaging examination will be assessed. Analysis of the primary outcome will be on an intention-to-treat basis.

**Discussion:**

If mesocolic excision in CD reduces postoperative disease recurrence and does not increase morbidity, this trial has the potential to change practice and reduce recurrence of CD after surgical resection.

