### End points

In total, patients will be followed for 5 years after surgery. The primary end point of the study is postoperative surgical recurrence. Surgical recurrence is defined as the requirement for repeat surgery for a CD-related indication caused by recurrent disease in the same anatomical areas. If reoperation is required it should be documented whether the reason is a specific CD-related complication, or a complication related to surgery in general (i.e., hemorrhage, intraperitoneal collection not amenable to conservative treatment, wound dehiscence, anastomotic leakage). CD-related indications for surgery include: (1) development of symptoms refractory to medical treatment; and (2) development of a complication caused by CD (i.e., fistula, perforation, and obstruction).

Secondary end points include assessment of endoscopic recurrence and clinical recurrence. Endoscopic recurrence will be assessed using the widely accepted Rutgeert’s score [15]. Only disease (Rutgeert’s score i2, or higher) proximal to the anastomosis or in the perianastomotic area is considered to be consistent with endoscopic recurrence. Disease in other sites will not be considered to be recurrence. Clinical recurrence is defined as the presence of endoscopic disease or radiological evidence plus the presence of symptoms attributable to CD that are severe enough to require medical or surgical treatment.

In addition, intra-operative complications and 30-day postoperative outcomes will be evaluated. These include estimated blood loss, duration of surgery, postoperative morbidity, reoperation rate, and the length of postoperative hospital stay. Postoperative complications will be recorded and classified based on the Clavien-Dindo classification [16].

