### Statistical analysis

Data will be presented as median (range), mean, and standard deviation for continuous variables, and percentages for categorical and ordinal data. In order to test whether there are differences between the two groups in the reduction of the primary and secondary outcome, Student’s *t* tests will be performed for continuous variables and chi-square or Fisher’s exact test for categorical variables. Those variables in which statistically significant differences are found will be introduced in the analyses as covariates. Kaplan-Meier analysis with log-rank statistics will be used to assess event-free interval and Cox forward conditional proportional hazards for regression analysis. We plan intention-to-treat analysis of the primary outcome. The full analysis set and per-protocol set will be used for the assessment of efficacy. Interim analyses will be done annually for the first 5 years after index surgery, and the sample size would be adjusted accordingly. An interim analyses will be performed to see if the trial should be continued or stopped, and so it serves as a safeguard. If the outcomes are very poor, more than would be expected, a clear-cut trend towards increased severe morbidity (classed as Clavien-Dindo grade 3 or greater) in relation to either the control or test group, the trial would be stopped and the enrolled participants would have been followed for outcomes and the primary analysis would have focused on the mortality end point. Alternatively, if there was a clear difference between the two groups in terms of benefits for the test cohort, with statistically significant findings emerging on comparison of one group over another that support uncontestable differences between groups, then it might also be stopped and all enrolled participants will be followed for outcomes and the primary analysis will focus on the efficacy end point. Data will be monitored by the treating clinicians and external independent trial monitoring committee, and the principle investigator of each participative site will take overall responsibility. An external independent trial monitoring committee will also analyze interim anonymized outcome data. All analyses considered a *P* value of ≤ 0.05 as statistically significant.

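### A non-significant difference test cannot support the condition that extensive mesenteric excision does not increase morbidity, in a trial sized on surgical recurrence alone

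*Protocol article*

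**What the plan says.** In the protocol article, the Discussion paragraph of the abstract sets out what result could alter practice: "If mesocolic excision in CD reduces postoperative disease recurrence and does not increase morbidity, this trial has the potential to change practice".

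Morbidity is an aim in its own right. The abstract's Background says of the trial: "It also aims to evaluate intra- and postoperative morbidity between the two approaches". The abstract's Methods place it among the secondary outcomes: "The secondary end points will be the postoperative endoscopic and clinical recurrence, and intra- and postoperative morbidity". Under End points, "intra-operative complications and 30-day postoperative outcomes will be evaluated", and "Postoperative complications will be recorded and classified based on the Clavien-Dindo classification".

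Under Statistical analysis, primary and secondary outcomes are compared between groups with Student's t test for continuous variables and "chi-square or Fisher’s exact test for categorical variables". The criterion is common to all of them: "All analyses considered a *P* value of ≤ 0.05 as statistically significant".

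Under Sample size, the calculation uses surgical recurrence at 60 months only (30% under limited excision, 20% decrease, 80% power, 5% significance). It gives 100 patients, raised to 116. No morbidity rate, tolerated excess or morbidity power appears.

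Statistical analysis and Cessation of trial add a separate provision: the trial stops if an evident trend to severe morbidity (Clavien-Dindo grade 3 or greater) appears in either arm. An external committee also analyses interim data.

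**The concern.** The first half of the condition, fewer recurrences, matches a test for a difference. The second half does not. To say that one operation does not increase morbidity is to say that any excess is smaller than some amount that matters, and a confidence bound is needed to support that. A P value above 0.05 shows only that the data did not establish a difference. In a small trial that result is common even when a real difference exists.

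This matters here because safety is the stated obstacle to the extensive operation. The main Background section says the mesentery is usually left behind largely because of bleeding concerns, with hematoma, continuing hemorrhage and injury to the mesenteric root as possible consequences. The main Discussion again names hematoma and hemorrhage as an anticipated challenge. Both sections already describe the approach as safe on preliminary or earlier data. A non-significant comparison could easily be taken as confirmation when the data remain compatible with a sizeable harm.

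**Working it through.** **Inputs from the protocol article**
- Total randomised: "will randomize patients (*n* = 116) scheduled to undergo primary ileocolic resection".
- Significance level: P ≤ 0.05, sidedness not stated.
- Primary assumptions: 30% against 10% surgical recurrence, 80% power.

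**Assumptions, because the article is silent**
- 1:1 allocation, so 116 / 2 = 58 per arm.
- Two-sided testing of morbidity.
- Control severe-morbidity rates of 5%, 10%, 15% and 20%.
- All 116 patients contribute 30-day data, which is favourable to the trial.

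**Step 1. The plan's own sample size.** The formula is n per arm = [z_α √(2p̄(1−p̄)) + z_β √(p1(1−p1) + p2(1−p2))]² / (p1−p2)², with p1 = 0.30, p2 = 0.10 and p̄ = 0.20.
- One-sided 5%: (1.645 × 0.5657 + 0.8416 × 0.5477)² / 0.04 = 48.4, so 49 per arm and 98 in total. This is close to the stated 100.
- Two-sided 5%: (1.960 × 0.5657 + 0.8416 × 0.5477)² / 0.04 = 61.6, so 62 per arm and 124 in total.
- Inflation: 100 × 1.10 × 1.05 = 115.5, so 116.

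The stated figures come from recurrence alone. Nothing in them depends on morbidity.

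**Step 2. Chance of missing a true doubling with 58 per arm.** The two binomial distributions were enumerated exactly. Power is the total probability of all tables with P ≤ 0.05 and the higher rate under extensive excision. The miss rate is 1 minus power.

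| Control rate → extensive-excision rate | Missed, chi-square | Missed, Fisher | n per arm for 80% power |
|---|---|---|---|
| 5% → 10% | 83% | 92% | 435 |
| 10% → 20% | 67% | 76% | 199 |
| 15% → 30% | 50% | 59% | 121 |
| 20% → 40% | 34% | 41% | 82 |

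Check by normal approximation for 10% → 20%: (0.10 × √58 − 1.96 × √(2 × 0.15 × 0.85)) / √(0.09 + 0.16) = (0.7616 − 0.9898) / 0.5 = −0.456. Power is Φ(−0.456) = 32%, so 68% is missed, in line with the exact 67%.

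**Step 3. What a non-significant result would leave open.**
- Observed 6/58 against 12/58: difference 10.3 points, chi-square P = 0.12, Fisher P = 0.20, Newcombe 95% CI −3.1 to +23.6 points.
- Observed 6/58 in both arms: difference 0, Newcombe 95% CI −11.8 to +11.8 points.

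**Step 4. Precision available.** With equal rates p, the 95% CI half-width is 1.96 × √(2p(1−p)/58). At 10% this is 1.96 × √(0.18/58) = 10.9 points.

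| Event rate in both arms | Half-width (points) |
|---|---|
| 5% | 7.9 |
| 10% | 10.9 |
| 15% | 13.0 |
| 20% | 14.6 |

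**Step 5. Illustration with an assumed tolerated excess of 10 points.** The article gives no such figure. Under true equality, the chance that the upper bound falls below 10 points is Φ(0.10/SE − 1.96). At a 10% rate, SE = 0.0557 and the chance is Φ(−0.165) = 43%. At 5%, 15% and 20% it is 70%, 33% and 27%.

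**The case against.** The strongest reply is that the article never adopts the rule at issue. The abstract sentence is a conditional remark about potential, not a success criterion. Morbidity is secondary and is to be evaluated, recorded and classified. The practice statement that closes the main Discussion rests on recurrence alone. A reader might infer that the protocol will treat P > 0.05 as proof of no increase, but no section says so. This part of the reply stands. What remains is that the article states a conclusion and a test, and the test cannot deliver the conclusion.

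A second reply is that margins and intervals for secondary outcomes usually belong in an analysis plan, which is not shown, and that trials sized on efficacy are rarely powered for safety. Both points are fair, so the absence of a margin or of power is not by itself the finding. Low power is acceptable where an outcome is only described. It becomes a problem where the outcome is made a condition for changing practice.

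A third reply is that morbidity has a further safeguard. A reader might infer that the P ≤ 0.05 comparison is the only morbidity rule, and that would be wrong: the stopping provision for grade 3 or greater complications exists, and so does the external committee. But that provision has no numerical threshold and governs whether the trial continues. Completing the trial without stopping would not show that morbidity was not increased.

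**Conclusion.** The point holds as a mismatch between a stated conclusion and the stated method. A non-significant morbidity comparison in this trial would not support a claim of no increase.

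The size depends on assumptions that the article does not supply: 1:1 allocation, two-sided testing and a severe-morbidity rate. Across control rates of 5% to 20%, a doubling is missed 83% down to 34% of the time with chi-square, and 92% down to 41% with Fisher. Power is below 80% throughout that range.

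Three stronger readings are not supported:
- That a doubling is missed about two times in three. This is true only for chi-square at a control rate near 10%, a figure found nowhere in the article.
- That non-significance is the most likely outcome of any doubling. At 20% against 40% both tests usually detect it.
- That a tolerated excess below about 11 to 12 points could never be excluded at a 10% event rate. That follows only if the observed rates are equal. Under true equality at 10%, the Newcombe upper bound falls below 10 points about 40% of the time.

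The mismatch itself does not depend on any particular rate.

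**What to change.** - For 30-day Clavien-Dindo grade 3 or greater, which can be derived from data already collected, report the risk difference (extensive minus limited excision) with its 95% confidence interval.
- State that a non-significant P value will not be read as no increase. That claim will be made only if the upper bound excludes an excess that the trial team specifies before seeing the data. Otherwise the comparison is reported as inconclusive.
- State the expected precision as an assumption: a 95% CI half-width of about 8, 11, 13 and 15 points at event rates of 5%, 10%, 15% and 20%, with 58 per arm.
- Reword the concluding sentence of the abstract's Discussion to match.

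The cost is a few lines of analysis wording and one interval, with no extra patients or data. The drawback is that the safety comparison may well have to be reported as inconclusive.

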**Trial registration:**

Clinical Trials.gov, ID: NCT03769922. Registered on February 27, 2019.

## Background

Disease recurrence at the site of the anastomosis after ileocolic resection for Crohn’s disease (CD) is of pivotal clinical importance. More than 90% of CD patients develop endoscopic recurrence, 20% of whom are symptomatic. Despite developments in biological therapy for CD, approximately 30–40% of patients require reoperation within the first 5 to 10 years. In addition to environmental factors, such as smoking and diet, the clinical pattern of disease, e.g., stricturing versus fistulating behavior, and pathological features of the resection margin, may also influence the risk of postoperative recurrence [1, 2].

Abnormal changes in the mesentery in patients with CD have been noted for several decades. Emerging data suggest that the mesenteric tissue plays an important role in the pathogenesis of CD [3–5]. A high value of visceral fat content [6], an increased mesenteric lymphatic-vessel density in the resection margin [7], and the presence of granulomata in the mesenteric lymph nodes have been found to be associated with postoperative recurrence [8].

Conventional surgical resection for CD does not usually involve resection of the associated mesentery, with traditional teaching advocating staying “close to the bowel wall.” To date, the inclusion of the mesentery in intestinal resection for CD has not become standard practice. This is largely due to technical concerns regarding risk of bleeding when handling tissues with significant inflammation, e.g., disease-related perforation, fistula formation, adhesions, and thickened mesentery [9, 10], which could lead to hematomas, ongoing hemorrhage, and injury to the mesenteric root [11, 12]. Therefore, despite recent interest in the role of the mesentery in CD, the implication of resection of the mesentery along with the diseased bowel has not been evaluated.

Our preliminary data indicate that: (1) extensive mesenteric excision is safe and feasible in surgical resection for CD; (2) inclusion of mesentery resection does not cause specific morbidity; and (3) extensive mesenteric excision results in reduced incidence of endoscopic recurrence after surgery (unpublished data). In addition, Coffey et al. reported that the inclusion of the mesentery in the course of ileocolic resection for CD is associated with reduced recurrence requiring reoperation [9].

To date, there has been no prospective trial comparing wide mesocolic resection with conventional surgery in CD. Thus, the objective of this multicenter, single-blind, randomized controlled trial is to determine whether there is a reduction in the rate of postoperative recurrence of CD following extensive mesenteric excision (EME), when compared to that of conventional limited mesenteric excision (LME) for ileocolic disease.

## Methods

### Study population

Patients with CD limited to the distal ileum and/or right colon receiving their index ileocolic resection are eligible for inclusion. Eligibility criteria include: age between 18 and 65 years with a documented history of CD based on endoscopic, radiological, or histological criteria. The exclusion criteria are: pregnancy or planning to become pregnant in the following year; CD located at a gastrointestinal site other than the terminal ileal cecum, or right colon; and intestinal fistula requiring resection of another segment of bowel. Eligible patients with perianal disease will be included. All participants will provide written informed consent. The schedule of enrollment, interventions, and assessment is presented in Fig. 1 (see also Additional file 1: Standard Protocol Items: Recommendations for Interventional Trials (SPIRIT) Checklist LME EME).

**Fig. 1 Fig1:**
[figure not shown]
Standard Protocol Items: Recommendations for Interventional Trials (SPIRIT) Flow Diagram of schedule of enrollment, interventions, and assessments

### Randomization

Given the nature of surgical procedures, it is not possible to blind the surgical team to the assigned treatment arm. However, patients will be blinded to the type of mesenteric excision performed. Eligible patients enrolled by each participating center will be randomized based on a computer-generated list maintained centrally. The randomization codes are uploaded on Google docs, and the study co-ordinator at each center will receive a link to the codes.. The group allocation will be conducted by a staff surgeon, or research assistant who is blind to the study by a sealed, opaque envelope. Individuals other than the surgical team involved in the trial will be blind to the assigned treatment arm according to the blinding guidelines indicated by Probst et al. [13].

After entering the abdomen, the surgeon will determine whether a hemostatic division of the mesentery is technically possible. If this is the case, as we would expect in the majority of patients, the envelope containing the randomization can be opened to find out what group the patient has been randomized to, and the operation proceeds as per the group allocation to either a mesenteric-based resection or conventional resection. If mesenteric division is not deemed possible, the patient will be excluded from the trial. The reasons for those that have not been randomized would be clearly reported. The number of excluded patient will be separately recorded. Alternatively, the patient may undergo initial stoma diversion followed by delayed resection with preoperative re-randomization in 6 months. This approach will be left to the discretion of the operating surgeon, while the reason for stoma creation should be documented. Patients undergoing delayed resection are, therefore, eligible for inclusion in the study.

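### Every center's co-ordinator has a link to the randomization codes while a judgement-based exclusion comes before the envelope is opened, so allocation concealment is not assured

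*Protocol article*

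**What the plan says.** All of the relevant text is in the Randomization section of the Protocol article.

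- Source of the sequence: patients are "randomized based on a computer-generated list maintained centrally".
- Access to it: "The randomization codes are uploaded on Google docs, and the study co-ordinator at each center will receive a link to the codes". The article describes no masking, patient-by-patient release, access restriction or access log.
- Concealment device: "The group allocation will be conducted by a staff surgeon, or research assistant who is blind to the study by a sealed, opaque envelope".
- Blinding: the section says that trial personnel outside the surgical team will not know which arm was assigned.
- Entry decision: "After entering the abdomen, the surgeon will determine whether a hemostatic division of the mesentery is technically possible". The envelope may be opened only if the answer is yes. Otherwise, "If mesenteric division is not deemed possible, the patient will be excluded from the trial".
- Alternative route: "the patient may undergo initial stoma diversion followed by delayed resection with preoperative re-randomization in 6 months", and "This approach will be left to the discretion of the operating surgeon".
- Record keeping: the number of excluded patients is recorded and the reasons for not randomizing are reported.

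The Abstract gives five recruiting sites in three countries.

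**The concern.** A sealed envelope conceals the next allocation only if nobody at the site can read the list from which the envelopes were filled. Here one person at each center is given a route to the codes. In many trials this would be a moderate weakness. In this one the last entry decision is made late and by judgement, with no objective criterion stated, and a negative answer removes the patient from the trial or defers them to a new randomization. If the next allocation is foreseen, that judgement can be influenced by it.

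The selection would occur before randomization. The excluded patients would not be in the analysis set, so the intention-to-treat analysis planned under Statistical analysis could not correct for them. The comparisons exposed are surgical recurrence and postoperative morbidity. The sections Statistical analysis and Cessation of trial also let severe morbidity or clear efficacy findings stop the trial, so those decisions would rest on the same comparisons.

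**Working it through.** No figure in the plan depends on this point, so there is nothing to reproduce. The check has two parts.

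**1. The statements side by side**

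- A centrally maintained list means that the sites do not hold the sequence. A link to the codes sent to each center's co-ordinator means that they can reach it. Without a stated restriction, the two do not agree.
- Co-ordinators are not described as part of the surgical team. If everyone outside that team is blind, the co-ordinators should be blind too, yet they are the people who receive the link.
- The feasibility check before opening the envelope is sound design when the sequence is hidden, because it keeps unsuitable patients from being randomized. The weakness lies in combining it with site access to the codes.
- Diversion followed by re-randomization, at the operating surgeon's discretion, is a second route by which a foreseen allocation could be avoided.

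**2. How large the distortion could be (illustration only)**

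From the documents: 30% surgical recurrence at 60 months with limited excision (Sample size), and 116 patients, taken as 58 per arm on the assumption of equal allocation. All other inputs are assumptions. The true effect is set to zero, so the limited arm stays at 30%, and patients are left out only when extensive excision is next.

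*Scenario A: every hostile case is left out.* A share s of patients has a hostile mesentery with 50% recurrence risk. The extensive-arm rate becomes (0.30 − s × 0.50) / (1 − s).

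- s = 0.10: 0.250 / 0.90 = 27.8%, a spurious 2.2 points
- s = 0.15: 0.225 / 0.85 = 26.5%, a spurious 3.5 points
- s = 0.20: 0.200 / 0.80 = 25.0%, a spurious 5.0 points

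*Scenario B: partial exclusion.* Half the patients are high-risk (45%) and half low-risk (15%), which averages to 30%. A fraction f of the high-risk patients due for extensive excision is left out. The extensive-arm rate is p_E = [0.5(1 − f) × 0.45 + 0.5 × 0.15] / [0.5(1 − f) + 0.5].

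For the type I error, let d = 0.30 − p_E and let p̄ be the mean of the two rates, with n = 58. Then se0 = √[2p̄(1 − p̄)/n], se1 = √[p_E(1 − p_E)/n + 0.30 × 0.70/n], and the rejection probability is Φ[(d − 1.96 se0)/se1] + Φ[(−d − 1.96 se0)/se1].

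| f | Extensive-arm rate | Spurious difference | Type I error (nominal 5%, two-sided) |
|---|---|---|---|
| 0.1 | 0.2775 / 0.95 = 29.2% | 0.8 points | 5.1% |
| 0.2 | 0.2550 / 0.90 = 28.3% | 1.7 points | 5.4% |
| 0.3 | 0.2325 / 0.85 = 27.4% | 2.6 points | 6.1% |
| 0.5 | 0.1875 / 0.75 = 25.0% | 5.0 points | 9.2% |

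For scale: if the 20% decrease in the Sample size section is read as absolute (30% to 10%), a 5-point distortion is 5/20, a quarter of the target difference, and 0.8 points is 0.8/20 = 4% of it.

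**The case against.** The strongest reply is that the text does not show concealment to be broken. The link goes to the co-ordinator, not to the surgeon who judges feasibility. The article does not say whether it opens the whole sequence, masked codes or only released entries, and access control may be set out in the full protocol. That stands as a limit on wording. A reader might infer that surgeons see the list, or that the envelope conceals nothing; the article says neither. It remains true that the article states a specific procedure giving site staff a route to the codes, and that this disagrees with its neighbouring sentences. That is more than an omitted detail.

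A reader might also infer that the surgeon who operates performs the allocation. The article says only "The group allocation will be conducted by a staff surgeon, or research assistant who is blind to the study", by sealed opaque envelope. It does not identify that surgeon with the operating surgeon, so nothing here rests on it.

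Nor is the direction of bias established. The Background ties bleeding concerns to including the mesentery, and the Discussion raises hematoma and hemorrhage with wide resection. Against this, the Discussion also says that using the mesenteric transition point reduces bleeding in the mesocolic approach, and the limited arm divides mesentery too. A bias favouring the extensive arm is plausible but assumed.

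Finally, exclusions and their reasons are already to be recorded. That makes selection partly visible afterwards. It does not prevent it.

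**Conclusion.** The point stands as a weakness in the stated procedure. Site access to the codes conflicts with central maintenance of the list and with the blinding of those outside the surgical team. Placed ahead of a judgement-based exclusion, it makes selective exclusion by foreseen allocation possible. Concealment is not assured; the documents give no evidence that it has been breached.

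Under the assumptions above, a treatment with no effect could show a difference from under 1 point, if few patients are left out, to about 5 points. The upper value needs either every hostile case left out whenever extensive excision is next, with 20% of patients hostile, or half of a large high-risk group left out. It is a ceiling for these scenarios, and reading it as the expected bias would go beyond the documents. Only the 30% rate and the total of 116 come from the article; the prevalence, the risks in the subgroups, the fraction excluded and the direction are all assumed. Confidence is high in the conflict between the statements and much lower in any particular size of bias. The change is worth making because no later analysis can restore concealment.

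**What to change.** - Withdraw the centers' access to the shared document.
- Keep the list with the central holder, independent of the sites, and release one allocation at a time by telephone or web, only after the feasibility decision has been logged with patient identifier and time. The feasibility judgement itself stays as it is.
- Extend the exclusion reporting already planned so that feasibility exclusions are given by site.
- Enrollment began on 1 February 2019 and the article appeared on 21 February 2020, so an amendment cannot protect patients already entered. For them, compare each feasibility exclusion with the code that was next in the sequence, examine the document's access history, and report both.
- Reword the Randomization section so that the statements on central maintenance, access and blinding agree.

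The cost is one amendment and a brief call or web step during the operation.
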